### How does Egyptian Arabic do gender?

Egyptian Arabic, a diglossic variation of Modern Standard Arabic (MSA), follows the same grammatical gender system as MSA. For the purpose of this experiment, there are no distinctions made between these two variants as role nouns and occupations are consistent across both.

Arabic follows a two-gender system with masculine [+masc] and feminine [+fem] distinctions, and importantly does not possess a ’neuter’ gender option. Similar to Indo-European languages with such a two-gender system (e.g., Spanish), the generic, unmarked, or default form which can be grammatically used to refer to women and men is the masculine. This masculine generic form is typically marked with no overt gender morphology. The feminine form, which is derived from the masculine, is syntactically marked using various morphemes, typically ‘*a(t)’* or ‘*a(h)’*. For animates (humans and various animals), gender assignment is based on semantic information (this information is often the biological sex of the noun) [12]. An example of this can be seen in (1) and (2) below where the ’ *a(h)*’ morpheme is used to transform the masculine noun into feminine. Importantly, this same relationship is also extended to the plural versions of these nouns. It is worth noting that plural masculine generics, relative to their singular counterparts, may be easier to interpret as a mixed-gender group. Despite being more overtly marked, the use of masculine plurals to refer to women in speech is not uncommon (e.g., *nurses* [+masc] to refer to a group of women), whereas the singular masculine would be uncommon in speech.

(1)مدرسmudaresteacher.M.SG’teacher[+masc]’(2)مدرسةmudares-**ah**teacher.F.SG’teacher[+fem]’

While this nominal agreement pattern is similar to many Indo-European languages, unlike Spanish, French, German, etc., Arabic requires gender and number agreement across pronouns, verbs, nouns and adjectives at the inflectional phrase level [12]. Consequently, gender marking is more salient and reinforced in Arabic than Spanish or German. Consequently, adopting gender-inclusive language in Arabic can be more costly and effortful as it would require a large amount of repetition to avoid the use of masculine generics.

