### Outcomes of interest

To answer the research questions outlined above, the study focuses on two outcome categories: fluency measures and the participant’s gender interpretation of the prime.

Fluency measures consist of 5 dependent variables: the total number of words produced, hesitation markers, number of false starts, fluency mistakes, and initial response time. These measures are consistent with current literature on speech production [34]. The focus on fluency allows for exploration of processing costs and benefits due to in/congruent or asymmetric stimuli. Additionally, fluency measures help show what is easily accessed or recalled. Processing benefits are expected when participants’ S-gender expectations are not violated (i.e., a *secretary* in feminine morphology and a *manager* in masculine morphology compared to a *secretary* in the masculine). Importantly however, roles associated with women presented in masculine morphology should *not* result in processing costs if masculine G-gender is truly interpreted as generic or unmarked.

To measure the participant’s interpretation of the prime their responses will be coded based on the proportion of gendered morphosyntactic markers in their speech. Importantly, this will be weighted at the tensed phrase (TP) level. This is to avoid inflating scores based on morphosyntactic markers for the sake of agreement across noun phrases or verb phrases. This coding will be used to derive two other categorical variables to be used in the analysis: the participant’s gender expectations and whether the expectations are congruent with the social stereotype associated with the prime.

Example 3 provides a fictitious response to the stimulus “*manager [+masc]*” and how this would be coded. Firstly, we can see that there are three morphosyntactic markers that are masculine, two of which are used only for agreement purposes. Secondly, we can determine that the participant interpreted the stimulus to be a man and that this response is congruent with the prime (i.e., grammatical gender and social gender are not asymmetric).

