For conditions with strict masculine or strict feminine G-gender: regardless of role stereo-typicality participants’ responses will be determined by the G-gender of the prime. In other words, the priming effect of G-gender will overpower the priming effect of social stereotype information and participants will strictly rely on G-gender rather than stereotype information to determine the S-gender of the referent. Further, this relationship will be more extreme in the singular compared to the plural (as the singular is less likely to be interpreted as generic compared to the plural). Consequently, it is expected that masculine generics will result in a male bias in perception and interpretation. Similarly, feminine G-gender **should** also result in female interpretation as this cannot be used generically. Importantly, if the masculine and feminine conditions behave similarly, this will confirm the notion that masculine generics are not actually generic in interpretation and are instead gender exclusive.

Further, it is expected that the neutral roles in the masculine generic condition will be more readily interpreted as stereotypically male and may also act as a ‘congruent’ condition. Therefore, participants’ responses towards ‘neutral’ roles (such as *student*) will mirror responses towards male-dominated roles.

In condition 3 (inclusive language), it is unclear how participants will interpret the stimuli. Firstly, due to the presence of gender-fair language, we would expect participants to use both feminine and masculine morpho-syntactic markers across all roles, with the neutral stereotype condition being the most compatible with this behaviour. In this scenario, participants will have shown that gender inclusive language can be used to overcome male bias in perception and increase the retrieval of female exemplars. Alternatively, participants’ gender expectations and interpretation of the prime may instead be determined by social stereotype information. In this case, we can determine that despite the presence of a feminine morphosyntactic marker in the stimulus and an increase in accessibility of female exemplars, gender inclusive language does not increase the retrieval of female exemplars in the presence of competing social stereotype information (i.e., a failure to overcome gender bias in perception because of social expectation).

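### All-masculine speech after a masculine prompt fits a generic reading as well as a male one, so markers alone cannot confirm that the masculine is not generic

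*Protocol article*

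**What the plan says.** **Measurement (Outcomes of interest).** Of the participants, the protocol says that "their responses will be coded based on the proportion of gendered morphosyntactic markers in their speech". Scores are weighted at the level of the tensed phrase, for this reason: "This is to avoid inflating scores based on morphosyntactic markers for the sake of agreement across noun phrases or verb phrases". Example 3, a fictitious response to the masculine form of *manager*, is said to contain "three morphosyntactic markers that are masculine, two of which are used only for agreement purposes". From it the authors conclude that "we can determine that the participant interpreted the stimulus to be a man".

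**Grammar (How does Egyptian Arabic do gender?).** "Arabic follows a two-gender system with masculine [+masc] and feminine [+fem] distinctions", and the section adds that there is no neuter. It also states that "the generic, unmarked, or default form which can be grammatically used to refer to women and men is the masculine", and that "Arabic requires gender and number agreement across pronouns, verbs, nouns and adjectives at the inflectional phrase level".

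**Target of inference (Definitions).** Male bias means a strictly male reading of a masculine form that in principle covers everyone. The contrast of interest is therefore male reading against generic reading.

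**Decision rule (Hypotheses).** "if the masculine and feminine conditions behave similarly, this will confirm the notion that masculine generics are not actually generic in interpretation". Table 5 gives a man as the only expected referent for the generic masculine, singular and plural alike.

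**A second route to the same question (Outcomes of interest).** Female-associated roles shown in the masculine should carry no processing cost if the masculine is truly generic.

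**The concern.** A measure of male bias has to come out differently under the two readings it is meant to separate. In the masculine conditions (1 and 1.1), an all-masculine response is the natural output of someone who pictures a man. On the grammar set out in the protocol, it is also the natural output of someone who takes the prompt as generic. The protocol has no code for the second possibility and resolves it as a man.

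The decision rule inherits the problem. Masculine markers after masculine prompts and feminine markers after feminine prompts is the pattern that agreement alone would give, so finding it cannot confirm exclusivity.

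Question 1a, whether singular masculine generics create a male bias and whether the plural differs, belongs to the stated primary objective. The study could report a male bias on the strength of markers that do not show one.

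**Working it through.** **Step 1. Reproduce Example 3.** The gloss carries three masculine marks: the pronoun, the verb and the adjective. The verb and adjective agree with the pronoun, so two are agreement-only, as the protocol says. Proportion masculine:

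- unweighted: 3/3 = 100%
- weighted by tensed phrase: (3 − 2)/(3 − 2) = 1/1 = 100%

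The weighting changes the count but not the proportion or the resulting code. The one marker left is the pronoun, which the grammar section lists among the agreeing forms.

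**Step 2. Set the readings side by side for a masculine prompt.**

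| Response | Under a strictly male reading | Under a generic reading |
|---|---|---|
| All masculine | expected | expected (masculine is the generic form; no neuter) |
| Mixed or feminine | not expected | possible |

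Only the second row separates the readings, and it can only count against male bias. For a feminine prompt there is no such ambiguity, because Hypotheses says the feminine has no generic use.

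**Step 3. How much an all-masculine response tells us.** Let *a* be the share of responses in which agreement or the default form fixes the gender. Let *q* be the chance of all-masculine marking in the remainder under a generic reading. Taking P(all masculine | male reading) = 1,

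likelihood ratio (male : generic) = 1 / [*a* + (1 − *a*)*q*].

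The documents give neither *a* nor *q*; both are assumptions, shown over a range.

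| *a* | *q* = 0.2 | *q* = 0.5 |
|---|---|---|
| 0 | 5.00 | 2.00 |
| 0.5 | 1.67 | 1.33 |
| 0.8 | 1.19 | 1.11 |
| 0.95 | 1.04 | 1.03 |
| 1 | 1.00 | 1.00 |

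For example, *a* = 0.8 and *q* = 0.5 give 1/(0.8 + 0.2 × 0.5) = 1/0.90 = 1.11. The nearer agreement comes to being obligatory, the nearer the ratio comes to 1. A larger sample does not alter this, because the ambiguity lies in the measure and not in its precision.

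**Step 4. Trials exposed.** Table 2 has four masculine prompts in each of blocks 1–3 and Table 3 has six masculine plurals in block 4. With the minimum of 30 participants per block:

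- singular: 3 × 30 × 4 = 360
- plural: 30 × 6 = 180, in the component labelled exploratory

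**Step 5. What the fluency contrast has to work with.** Female-stereotype roles appear in the singular masculine once in block 1, twice in block 2 and once in block 3: 30 × 1 + 30 × 2 + 30 × 1 = 120 trials. The analysis plan already includes the stereotype-by-language interaction needed to use them.

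**The case against.** A reader might infer something stronger: that every masculine-marked response is coded as a man, that agreement forces masculine speech, and that a male bias would be found whether or not it exists. The documents do not support this.

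- **No such coding rule is stated.** The outcome is a proportion, mixed responses are possible, and Example 3 is one wholly masculine illustration. An article may leave cut-offs to a coding manual.
- **Agreement with the prompt is not shown to be compulsory.** The rule is given at the level of the inflectional phrase, while the prompt is a bare noun that participants may not repeat. The protocol also says gender for animates rests on semantic information. A speaker who pictures a female nurse may switch to the feminine, and that would be informative.
- **A share near 100% under both readings is an assumption.** With *a* = 0 the ratio in the working is 2 to 5, so markers would then carry some information.
- **Condition 2 is sound.** With no generic use of the feminine, coding a feminine response as a woman has no rival explanation.
- **The plan is not without a discriminating test, and no outcome is named primary.** Fluency bears on the same question, and similar behaviour in Hypotheses need not mean markers only.
- **The singular has some support.** The protocol says the singular masculine is uncommon in speech about women.

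All of this stands, and it limits the point to conditions 1 and 1.1 and to inferences drawn from markers. It does not rescue the inference itself. The possibility of switching makes feminine markers informative; it does not make all-masculine speech proof of a male reading. The remark about the singular concerns women as referents and does not cover a person of unspecified gender, which is the generic case. For the plural, the protocol says that use for women is not uncommon, which weakens the inference further.

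**Conclusion.** The concern holds in limited form. In the masculine conditions, all-masculine markers are compatible with both a generic and a strictly male reading. Neither the conclusion drawn in Example 3 nor the claim of confirmation in Hypotheses is sound where it rests on markers. Feminine or mixed markers remain useful evidence against a strictly male reading.

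The exposure is 360 singular and 180 exploratory plural trials at the planned minimum sample; how many would be misread cannot be known from the protocol. How weak the evidence is depends on how far speakers follow the prompt's gender: the likelihood ratio is about 1.03 to 1.04 if agreement or default fixes 95% of responses, and 1.33 to 1.67 if it fixes half. The qualitative conclusion needs only the protocol's own grammar: masculine as the generic form, no neuter, and agreement that includes pronouns.

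**What to change.** Settle these points before responses are coded:

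1. In conditions 1 and 1.1, code an all-masculine response as masculine-marked (male or generic). Reserve the code for a man for responses that carry independent referent gender, such as a lexically gendered noun or a named person. Amend Example 3 to match.
2. Keep the coding as a woman in condition 2.
3. In Hypotheses, replace the claim of confirmation with a statement that parallel marker patterns in the masculine and feminine conditions are compatible with agreement alone.
4. Base the generic-versus-male conclusion for question 1a on the planned fluency contrast for female-stereotype roles in the masculine, through the stereotype-by-language interaction, with markers as supporting evidence.

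The cost is in coding and analysis wording; no new data are needed. The price is fewer definite codes for a man in the masculine conditions and a more cautious conclusion from markers. The fluency contrast also needs care in interpretation: Materials says the female-stereotype roles occur more often in the feminine, so the lower frequency of their masculine form is a rival explanation for any cost observed.

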**Table pone.0292936.t005:** 

(3) هو بيكون المسؤول		
huwa	biko:n	mas2o:l
he.GEN.**M**.3SG	3PROG.**M**.is	DEF.responsible.**M**.SG.ADJ
‘He is [+masc] responsible [+masc]’		

### Hypotheses

As seen in Table 5 predictions for the directional relationships of the independent and dependent variables are made. These predictions are described and motivated in greater detail below.

**Table 5 pone.0292936.t006:** Directional relationships between independent and dependent variables.

VARIATION			OUTCOMES						
between	within		gender interpretation		fluency				
condition	association and number		referent expectations	proportion of gendered morphosyntactic markers	no of words produced	fluency mistakes	number of false starts	hesitation markers	initial response time
1. Generic masculine	man	SG	man	high proportion of masculine morphosyntactic markers	high	low	low	low	low
		PL							
	woman (incongruent)				low	high	high	high	high
	neutral				high	low	low	low	low
2. Feminine G-gender	man (incongruent)		woman	high proportion of feminine morphosyntactic markers	low	high	high	high	high
	woman				high	low	low	low	low
	neutral				high	low	low	low	low
3. Gender fair language (fem/masc)	man		interpretations can be a) mixed group b) congruent with stereotype	presence of both feminine and masculine morphosyntactic markers with higher proportion of masculine	no significant differences for stereotype or number variation				
	woman								
	neutral								
4. English gender neutral	man		man	presence of feminine, masculine, or neutral pronouns depending on stereotype	no significant differences for stereotype or number variation				
	woman		woman						
	neutral		unknown						

For conditions with strict masculine or strict feminine G-gender: regardless of role stereo-typicality participants’ responses will be determined by the G-gender of the prime. In other words, the priming effect of G-gender will overpower the priming effect of social stereotype information and participants will strictly rely on G-gender rather than stereotype information to determine the S-gender of the referent. Further, this relationship will be more extreme in the singular compared to the plural (as the singular is less likely to be interpreted as generic compared to the plural). Consequently, it is expected that masculine generics will result in a male bias in perception and interpretation. Similarly, feminine G-gender **should** also result in female interpretation as this cannot be used generically. Importantly, if the masculine and feminine conditions behave similarly, this will confirm the notion that masculine generics are not actually generic in interpretation and are instead gender exclusive.

Further, it is expected that the neutral roles in the masculine generic condition will be more readily interpreted as stereotypically male and may also act as a ‘congruent’ condition. Therefore, participants’ responses towards ‘neutral’ roles (such as *student*) will mirror responses towards male-dominated roles.

In condition 3 (inclusive language), it is unclear how participants will interpret the stimuli. Firstly, due to the presence of gender-fair language, we would expect participants to use both feminine and masculine morpho-syntactic markers across all roles, with the neutral stereotype condition being the most compatible with this behaviour. In this scenario, participants will have shown that gender inclusive language can be used to overcome male bias in perception and increase the retrieval of female exemplars. Alternatively, participants’ gender expectations and interpretation of the prime may instead be determined by social stereotype information. In this case, we can determine that despite the presence of a feminine morphosyntactic marker in the stimulus and an increase in accessibility of female exemplars, gender inclusive language does not increase the retrieval of female exemplars in the presence of competing social stereotype information (i.e., a failure to overcome gender bias in perception because of social expectation).

Similarly, in condition 4 (neutral English), stereotypical information may inform participants’ gender expectations, such that *doctors* are more likely to be men and *secretaries* are more likely to be women in responses. If this is the case, then the fixed effect for language in conditions 3 and 4 should not be statistically different. Importantly, in this condition participants have the option to respond in the gender neutral ‘they’ instead of assuming the role’s gender. Therefore, some variation between feminine, masculine, and neutral pronouns could be expected. If this condition also elicits highly gendered responses based on social stereotypes, then this presents evidence on the importance of gender-fair and representative language rather than just neutral language. This has implications for jobs advertised in English, which are assumed to be gender-neutral in interpretation but may instead entrench participant’s existing stereotypes.

Additionally, it is expected that fluency measures in congruent conditions will exhibit processing benefits (i.e., fewer fluency mistakes, more speech produced within the time limit, less hesitation, and reduced lag time) compared to their incongruent counterparts. Where grammatical information and stereotype information are incongruent (i.e., *nurse* presented in the masculine or *manager* presented in the feminine), it is predicted that outcomes related to fluency and initial response time will be negatively affected and participants will experience processing costs as a result of a violation of expectations. Importantly, interpreting masculine G-gender as generic should not be as costly or inefficient because it can be used to refer to male or female S-genders.

Further, condition 3 should not show significant differences in fluency or response time due to stereotype or number variation. This is because G-gender and stereotype information can always be congruent in a word-pair. Similarly in condition 4, it is predicted that fluency and response time will not vary across stereotype or number.

It is worth noting that condition 3 (inclusive language) as a whole compared to other conditions may trigger longer response times and processing costs because the word-pair may lead to initial hesitation as to which form of gender agreement the participant should select given that both the masculine and feminine are presented. Additionally, fem/masc combinations are not as frequent as masc/fem combinations and so some order effects/lag time are expected in this condition. This condition may also elicit plural morpho-syntactic markers if participants interpret the word pair as having both one male and one female referent.

Similarly, condition 2 (feminine G-gender) as a whole is likely to show processing costs, as role nouns associated with men or those that are neutral are lower frequency in the feminine compared to their masculine counterparts. That being said, both the feminine and masculine versions of a role noun share identical root morphemes and vary only in suffixes so differences in fluency can directly be attributed to the infrequent use of feminine role nouns. Consequently, the English version of the experiment, and masculine generic conditions in Arabic are expected to trigger higher fluency scores compared to the other conditions.

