## Materials

Experimental stimuli and role nouns have been selected based on a corpus collected from online Egyptian recruitment websites [11] and a large scale norming study on occupational stereotypes [35]. These roles were then cross-checked on Sketch Engine to ensure that none of the roles selected are low frequency. For an occupation to qualify as stereotypically female, it has to be typically advertised to women and advertised in feminine grammatical gender (such as *nurse* and *secretary*). Similarly, these roles on Sketch Engine were more likely to appear in feminine G-gender compared to their masculine counterpart, which further validates the stereotypicality of the role. For stereotypically male roles, the same approach was adopted, and occupations were selected if they mostly (at least 70%) targeted men and used masculine grammatical gender (such as *lawyer* and *manager*).

There were two main challenges when selecting the experimental stimuli. Firstly, the gendered stereotypes need to hold cross-culturally for both Egyptian and British participants. Secondly, as the existing corpus and literature has shown, Egyptian online recruitment is heavily gender segregated and polarised. Consequently, finding ‘neutral’ roles in the corpus proved to be difficult and therefore 3 of the neutral stimuli were selected based on other norming studies’ classifications [3, 35].

To mitigate these challenges and ensure that the stereotypes match the attitudes of the target sample(s), additional norming during the piloting stage will be conducted. This will consist of a simple questionnaire to be circulated amongst an Egyptian and British sample (n = 10 for each) asking participants to rate the occupations selected (this includes 4 plus an additional 2 ‘back-up’ role nouns in each stereotype) as stereotypically male, female, or neither on a 7-point scale. Role nouns with stereotypes that do not hold cross-culturally will be excluded from the experiment, with the target of having 4 occupations for each stereotype.

Non-experimental stimuli will include animals (such as *cat*) and will be G-gender balanced with 2 nouns presented in feminine G-gender and 2 presented in masculine G-gender.

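### For fluency and response time, the incongruent form of a stereotyped noun tends also to be its rarer form, so an incongruence cost may be partly or wholly a rare-word cost

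*Protocol article*

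**What the plan says.** All references are to the Protocol article.

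- **Hypotheses, incongruent items.** Where grammatical and stereotype information conflict, "participants will experience processing costs as a result of a violation of expectations". A manager in the feminine and a nurse in the masculine are the examples.
- **Hypotheses, condition 2 as a whole.** Costs are also expected because "role nouns associated with men or those that are neutral are lower frequency in the feminine compared to their masculine counterparts". Since the two forms share a root, the text concludes "so differences in fluency can directly be attributed to the infrequent use of feminine role nouns".
- **Outcomes of interest.** Roles associated with women, shown in the masculine, "should *not* result in processing costs if masculine G-gender is truly interpreted as generic or unmarked". A cost in that cell would therefore count against a generic reading.
- **Materials, female roles.** They had to be advertised to women in feminine grammatical gender, and "these roles on Sketch Engine were more likely to appear in feminine G-gender compared to their masculine counterpart".
- **Materials, male roles.** "For stereotypically male roles, the same approach was adopted, and occupations were selected if they mostly (at least 70%) targeted men" and used the masculine.
- **Materials, frequency screen.** "These roles were then cross-checked on Sketch Engine to ensure that none of the roles selected are low frequency". The screen is described for roles. No matching of masculine and feminine forms is stated.
- **Pre-specified analysis plan.** Language condition is the fixed effect and its interaction with stereotype is explored. By-item random intercepts and slopes are meant to cover stimulus length and familiarity with the occupation.

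**The concern.** For male roles in the feminine, the protocol names two causes of one expected cost. The shared root excludes differences between occupations as the explanation. It does not favour rarity over violated expectation, or the reverse.

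The wider difficulty is that noun selection makes the two causes run together. The planned random effects do not undo this. By-item intercepts absorb how familiar an occupation is. By-item slopes let nouns scatter around an average language effect. A shift in the same direction in every stereotyped noun remains in the average and appears in the stereotype-by-language interaction.

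At stake are research question 1c, on processing costs and benefits, and the fluency inference about genericity in Outcomes of interest. If the masculine form of a female-stereotyped noun is simply less often met, a cost in that cell could appear even though readers accept the masculine as generic.

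**Working it through.** **Plan's own figure.** 4 × 30 + 30 + 30 = 180, as stated under Sample size. Blocks 1–3, which carry the singular Arabic contrast, supply 3 × 30 = 90. No effect size is stated.

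**Coding.** Table 2 shows each of the 12 nouns once in the masculine, feminine and word-pair forms across blocks 1–3. Take the singular masculine and feminine forms only. *Incongruent* follows Table 5: male role in the feminine, female role in the masculine. *Rarer* follows Hypotheses (male and neutral nouns: the feminine) and Materials (female nouns: the masculine).

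| | commoner form | rarer form |
|---|---|---|
| congruent, 8 stereotyped nouns | 8 | 0 |
| incongruent, 8 stereotyped nouns | 0 | 8 |
| neutral nouns, not incongruent | 4 | 4 |

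Among stereotyped nouns the correlation is 1.00, and none of the congruence variance is independent of this two-level frequency code. With the neutral nouns added (24 forms), the covariance is 8/24 − (8/24)(12/24) = 1/6 and the correlation is (1/6) / √(2/9 × 1/4) = 0.71.

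**What neutral nouns add.** Let D be the feminine-minus-masculine difference within a noun, averaged over each noun type. Let f be a general feminine effect, c the congruence effect and r the rare-form effect:

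- male nouns: D_M = f + c + r
- female nouns: D_F = f − c − r
- neutral nouns: D_N = f + r

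Hence c = D_M − D_N. The separated congruence effect uses male and neutral nouns only. Female nouns in the masculine contribute nothing to it, because c and r always enter D_F together.

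Share of congruence variance left after frequency:

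- Noun effects only: sums of squares of the differences are 8 (congruence) and 12 (frequency), with cross-product 8. So 1 − 8²/(8 × 12) = 33%.
- Noun and feminine effects: removing the mean of 1/3 leaves frequency differences of 2/3, −4/3 and 2/3, with sum of squares 10.67 and cross-product 8. So 1 − 8²/(8 × 10.67) = 25%.

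**Consequence if only rarity matters.** Assume independent responses with residual SD 1, no slope variance, c = 0, and a two-sided test at 0.10. The 0.10 is the level given under Sample size for the later power analysis; its sidedness is not stated. From Table 2, the congruent/incongruent items per participant are 4/2 in block 1 and 2/3 in blocks 2 and 3. The variance of a participant's mean difference is 1/4 + 1/2 = 0.75 in block 1 and 1/2 + 1/3 = 0.83 in blocks 2 and 3, averaging 0.81. The standard error is √(0.81/90) = 0.095.

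For a rare-form cost of 0.2, z = 0.2/0.095 = 2.1 against a critical value of 1.645, a rejection probability of about 68%. Simulation (2,000 runs per cost, participant-mean differences) agrees:

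| assumed rare-form cost (SD) | congruence estimate | significant |
|---|---|---|
| 0.1 | −0.10 | 29% |
| 0.2 | −0.20 | 68% |
| 0.3 | −0.30 | 94% |
| 0.5 | −0.50 | 100% |

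The contrast returns the whole rare-form cost as a congruence effect.

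**Consistency of the neutral check.** Table 5 predicts high fluency and short response time for neutral nouns in the feminine. The text on condition 2 predicts costs, naming neutral nouns among those rarer in the feminine. If Table 5 is only a ranking within a condition, it does not say so. Hypotheses also suggests that neutral nouns in the masculine may behave as congruent, in which case D_N would carry some expectation effect too.

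**The case against.** **The two attributions answer different questions.** The frequency sentence concerns condition 2 as a whole, which is a language main effect. The expectation sentence concerns incongruent against congruent items, which is an interaction. This stands: they collide only for male nouns in the feminine. For female nouns in the masculine the problem comes from the Materials section, not from two competing sentences.

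**A reader might infer that the study's case on masculine generics falls.** The documents do not support that. Hypotheses also tests genericity by whether the masculine and feminine conditions behave alike in referent interpretation, measured by gendered markers in the responses. This confound does not reach those outcomes.

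**A reader might infer that the causes cannot be separated at all.** That is too strong. Neutral nouns separate them partly on the feminine side, and a graded frequency measure could separate more than the two-level code used here.

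**A reader might turn the 70% rule into a frequency ratio and then a percentage slowing.** The rule describes whom recruitment advertisements targeted, not how often a form occurs in a corpus. The documents give no slope of response time on frequency, so no such percentage is offered.

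**The simulation puts in the cost it finds.** True. It shows how the contrast would behave, not that a rare-form cost exists.

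**The task may mute rarity.** The prompt is played, stays on screen and must not be repeated, so participants need not retrieve it. This stands in part: a recognition cost bears most plausibly on initial response time, less clearly on the other four measures.

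**Frequency may be part of the stereotype.** Materials treats the dominant form as supporting evidence for stereotypicality, so adjustment may remove some of the effect sought. This stands and shapes the remedy.

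**A fuller analysis plan may name a frequency covariate.** It may. The point rests on the stated selection approach and the stated attribution, not on that omission.

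**Conclusion.** The concern holds for the fluency and response-time outcomes. Congruence is largely aligned with relative form frequency, and completely so for the eight stereotyped nouns on a commoner/rarer coding. The planned item effects do not remove the average shift. Including neutral nouns leaves 25% to 33% of the congruence variance independent of frequency, on the feminine side only and assuming that rarity costs the same for neutral and male nouns. The test of female roles in the masculine has no such internal check.

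The actual bias cannot be sized, because no form frequencies are given. The 29% to 100% above is conditional on assumed costs of 0.1 to 0.5 SD. What is settled is that the direct attribution to infrequent use is unsupported, and so would be an equally direct attribution to violated expectation.

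**What to change.** 1. Look up the corpus frequency of each exact form shown: 12 nouns × 2 singular forms = 24, plus the 6 plural masculines in Table 3, so 30 look-ups in the corpus tool already used. Repeat for any noun replaced after norming.
2. For the fluency models, above all initial response time, report the congruence contrasts with and without log form frequency, as a sensitivity analysis.
3. Report the neutral-noun feminine-versus-masculine contrast as a frequency benchmark, and first reconcile Table 5 with the text on condition 2 for that cell.
4. Delete the direct attribution in Hypotheses. State that a fluency cost which disappears on adjustment cannot be assigned to either violated expectation or form frequency, and is not by itself evidence that the masculine is not generic.

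**Cost.** The look-ups, one covariate and a few sentences, with no change to design or sample. The two variables are strongly correlated and frequency may partly reflect the stereotype, so the adjusted contrast will be imprecise and may over-adjust. It should qualify the expectation claim, not be its only gate.
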